##### Assessment of school lunch uptake and food sales

To assess school lunch uptake, schools will be asked to provide their routinely collected school meal uptake data. To assess school food sales, we will request weekly aggregated food sales data for two prespecified months in the previous year. Most schools use online payment management systems, which provide sales data by types of food/drinks sold. We will extract data on the number of items sold for both SFS restricted food/drinks (including sugar-sweetened beverages, confectionery, fried food, snacks and so on) and predefined healthy foods and compare sales of these food categories across schools, taking into account school size and school lunch uptake.

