## Abstract

**Introduction:**

Excess free sugar intake is associated with obesity and poor dental health. Adolescents consume substantially more free sugar than is recommended. National (UK) School Food Standards (SFS) are in place but are not mandatory in all schools, and their impact on the diets of secondary school pupils is unknown. We aim to evaluate how SFS and wider healthy eating recommendations (from the national School Food Plan (SFP)) are implemented in secondary schools and how they influence pupils’ diets and dental health.

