**Methods and analysis:**

Secondary-level academies/free schools in the West Midlands, UK were divided into two groups: SFS mandated and SFS non-mandated. Using propensity scores to guide sampling, we aim to recruit 22 schools in each group. We will compare data on school food provision and sales, school food culture and environment, and the food curriculum from each group, collected through: school staff, governor, pupil, parent surveys; school documents; and observation. We will explore the implementation level for the SFS requirements and SFP recommendations and develop a school food typology. We aim to recruit 1980 pupils aged 11–15 years across the 44 schools and collect dietary intake (24-hour recall) and dental health data through self-completion surveys. We will compare free sugar/other dietary intake and dental health across the two SFS groups and across the identified school types. School type will be further characterised in 4–8 case study schools through school staff interviews and pupil focus groups. Evaluation of economic impact will be through a cost-consequence analysis and an exploratory cost–utility analysis.

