## Introduction

Excess sugar consumption is a major contributor to increased energy intake/obesity, adverse cardiometabolic health^1^ and poor dental health.^2^ UK adolescents consume three times their recommended amount of total energy intake from free sugars^3^; almost half of 15- year-old individuals have dental caries^2^ and nearly a third have excess weight.^4^ Adolescence is an important time for dietary intervention as it is a key period for establishing dietary patterns,^5^ with greater autonomy over dietary decisions. A large proportion of adolescent dietary intake occurs while at school, making these opportune settings for intervention.

In the UK, a longstanding strategy for improving children’s diet has been nutritional standards for school food. School meal standards were first introduced in 1941, but fell out of favour later in the 20th century. In 2006, following a national school meal review,^6^ national School Food Standards (SFS) were relaunched in England and became a legal requirement for most state schools. In 2015, a Department for Education (DfE) SFS review resulted in substantial changes. For ease of implementation, nutrient-based standards were removed while retaining food-based standards underpinned by a nutrient framework.^7^

In addition to the national SFS, the School Food Plan (SFP) was launched in 2013, providing a wider set of non-statutory recommendations for schools that promote a ‘whole school’ approach to healthy eating.^8^ One central aim was to increase school meal uptake, as higher demand enables better quality meals to be served at a lower cost. Another aim was to provide practical support, advice and information for headteachers to help improve the quality and uptake of their school’s food. In addition to school food provision, the plan addresses how healthy eating can be incorporated within all aspects of school life and the wider community.^9^

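### The only stated comparison of food sales takes account of school lunch uptake, which the School Food Plan aims to raise, so it need not show the overall difference in sales between schools

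*Protocol article*

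**What the plan says.** Under the heading Assessment of school lunch uptake and food sales, the article sets out two data requests. On uptake: "To assess school lunch uptake, schools will be asked to provide their routinely collected school meal uptake data". On sales: "we will request weekly aggregated food sales data for two prespecified months in the previous year". The sales measure is a count: "We will extract data on the number of items sold for both SFS restricted food/drinks", with a matching count for healthy foods defined in advance. The plan is then to "compare sales of these food categories across schools, taking into account school size and school lunch uptake". No other sales comparison is stated, and the article does not say whether uptake enters as a denominator, a covariate or a stratifier.

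The Introduction says of the SFP: "One central aim was to increase school meal uptake, as higher demand enables better quality meals to be served at a lower cost". It also describes the SFP recommendations as non-statutory. The Abstract puts both policies within the evaluation: "We aim to evaluate how SFS and wider healthy eating recommendations (from the national School Food Plan (SFP)) are implemented in secondary schools". It also names sales among the things compared by School Food Standards (SFS) group: "We will compare data on school food provision and sales, school food culture and environment, and the food curriculum from each group".

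**The concern.** Uptake lies downstream of at least one of the two policies under study. A comparison of sales at a given level of uptake removes whatever part of the sales difference runs through uptake. It answers a narrower question: do schools sell fewer restricted items for the amount of catering they do? That is a sensible question, but it is not whether the schools sell fewer restricted items overall.

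With only the uptake-adjusted figure, a reader cannot tell fewer restricted items sold from more lunches taken. Two groups of schools with the same sales per pupil could be reported as different. Two groups that do differ per pupil could be reported with the difference shrunk, enlarged or reversed. The same applies to the healthy-food categories.

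**Working it through.** The article gives no figure for the sales comparison and no uptake level, so there is nothing to reproduce. All inputs below are assumptions chosen to show the mechanism. Comparisons are between schools at one time, as in the plan.

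**Uptake as denominator.** Let *s* be items sold per pupil on roll and *u* the proportion taking school lunch. Sales per lunch are *s/u*. If *s* is the same in both groups, the ratio of the higher-uptake to the lower-uptake group is *u0/u1*.

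Worked case, 1000 pupils per school and 200 restricted items a day in each:
- 40% uptake: 200/400 = 0.50 per lunch.
- 50% uptake: 200/500 = 0.40 per lunch.
- Ratio 0.40/0.50 = 0.80, an apparent 20% lower figure, although both schools sell 200/1000 = 0.20 per pupil.

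The same formula over a range of uptake:

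| Uptake compared | Ratio u0/u1 | Apparent difference |
|---|---|---|
| 40% vs 42% | 0.952 | -4.8% |
| 40% vs 45% | 0.889 | -11.1% |
| 40% vs 50% | 0.800 | -20.0% |
| 40% vs 60% | 0.667 | -33.3% |
| 50% vs 55% | 0.909 | -9.1% |
| 50% vs 60% | 0.833 | -16.7% |

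The direction can also differ. Compare a school with 40% uptake and 200 items with one at 30% uptake and 160 items, both with 1000 pupils. Per pupil the second is lower: 0.16/0.20 = 0.80, or -20%. Per lunch it is higher: (160/300)/(200/400) = 0.533/0.50 = 1.07, or +7%.

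**Uptake as covariate.** Suppose that within groups sales per pupil vary as *u* to the power *b* (the elasticity), and that the groups have equal sales per pupil overall. The expected adjusted ratio is then about (*u0/u1*) to the power *b*. For 40% vs 50% this is 1.00 at *b* = 0, 0.80^0.5 = 0.89 at *b* = 0.5 and 0.80 at *b* = 1.

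A simulation agrees. It used 22 schools per group, uptake of 40% in the lower group with SD 10 points, residual SD 0.3 on the log scale and 2000 runs per scenario. Log sales per pupil were regressed on group and log uptake.

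| Uptake gap | Elasticity | Adjusted ratio | Runs significant at 5% |
|---|---|---|---|
| 5 points | 0 | 1.00 | 5% |
| 5 points | 0.5 | 0.95 | 9% |
| 5 points | 1 | 0.89 | 23% |
| 10 points | 0 | 1.00 | 5% |
| 10 points | 0.5 | 0.90 | 18% |
| 10 points | 1 | 0.80 | 56% |

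The ratio of sales per pupil without uptake adjustment stayed between 1.00 and 1.02 throughout. So the adjusted and overall figures agree when uptake does not differ, or when sales do not depend on uptake, and part company otherwise.

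**The case against.** Several objections have force.

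- **The method is open.** Taking uptake into account could mean a denominator, a covariate, stratification or figures set side by side, and a condensed article may leave the model to a fuller document. This stands, and it is why no single size can be given. But naming uptake as something to condition on is a stated choice, and under either usual reading it can separate the adjusted figure from the overall one.
- **The SFP is not the mandate.** The two groups are defined by whether the SFS are legally required. Raising uptake is an aim of the non-statutory SFP, and no passage says that the mandate changes uptake. This stands. A reader might infer that the mandated versus non-mandated sales comparison is biased. The article does not support that without evidence that uptake differs between those groups.
- **Sales are an implementation measure.** They sit with the data on implementation and school context, and are not among the pupil outcomes, where intake is measured directly. No passage says that the sales comparison is meant to show pupils' exposure to restricted items, so per-lunch sales cannot be called the wrong quantity on that ground.
- **Sales per pupil can mislead too.** A school where most pupils bring packed lunches looks better simply because few buy anything, and uptake may differ for reasons unrelated to policy. This stands, and it argues for reporting both figures. Against it, the propensity score already carries some prior differences (free school meal eligibility, area deprivation, roll size).
- **Uptake is already assessed.** The data are collected, but the article does not say that uptake will be compared between groups as a result.

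A reader might also speak of a fall in sales. The data are two months from the previous year, compared across schools with no pre-policy baseline, so only differences between schools can be described.

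**Conclusion.** The point holds in a limited form. The one sales comparison the article states conditions on a quantity that the SFP, whose implementation is under evaluation, aims to raise. Where uptake differs between the schools compared, the result should not be read as the overall difference in sales.

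The size is unknown. Over the assumed uptake gaps of 2 to 20 points, the apparent difference with equal sales per pupil runs from about 5% to 33% if uptake is the denominator. As a covariate, with gaps of 5 and 10 points, it runs from nil to about 20%. It is nil if uptake does not differ.

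The concern is strongest for comparisons by degree of SFS/SFP implementation or by school type. It does not touch the primary or secondary pupil outcomes or the sample size.

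**What to change.** In the section on school lunch uptake and food sales, state that:

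1. sales of restricted and healthy items per pupil on roll, adjusted for school size and propensity score but not for uptake, will be compared and reported alongside the uptake-adjusted or per-lunch figure;
2. school lunch uptake will be compared between the same groups as an outcome in its own right;
3. an uptake-adjusted difference will not be interpreted as the overall effect on sales.

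It would help to say at the same place how uptake enters the adjusted figure. Sales, uptake and roll size are already requested or held, so the cost is a few lines of wording and one extra analysis. The downside is that sales per pupil will vary more between schools, because uptake varies, and so will be estimated less precisely.

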##### Assessment of school contextual factors

We will collect data on a variety of contextual factors through observation; school document review; and the staff, governor, pupil and parent surveys, with further exploration in the second phase case studies. These factors include: the physical school environment; school leadership and organisational culture; the influence of governors; staff knowledge and skills; school engagement with parents; and school financial considerations. In addition, socioeconomic and demographic characteristics of the pupil population will be assessed through routinely available school data. Information on SFS voluntary sign up will also be requested from non-mandated schools.

##### Data capture on SFS/SFP resource use

Food provision costs will be estimated from a detailed list of resources obtained through a school staff survey, 1-day researcher observation, catering contracts, and school menus and pricing. Wider costs associated with SFP implementation will be obtained from school staff, parent and pupil surveys and observation. Each resource use item will be costed using financial data supplied by the school or obtained from the published literature.

##### Pupil outcome data collection

We aim to compare dietary intake and dental health in pupils in the two defined SFS school groups. The primary outcomes are intake of free sugars (grams): (1) during school day lunch (determined by asking pupils when they ate their lunch); (2) while at school; and (iii) during the full 24-hour period of the same school day. Secondary dietary outcomes include: percentage of dietary energy intake from free sugars; total energy intake (kcal); total fat intake (grams); fibre intake (grams); number of sugar-sweetened beverages consumed; number of sugar and chocolate confectionery items consumed; number of foods high in fat, sugar and salt consumed; and number of fruit and vegetable portions consumed. These outcomes will also be compared across the two school groups for the three defined time periods (school day lunch; while in school; over 24 hours). Additional secondary dietary outcomes are: free sugar intake providing >5% energy intake; number of eating/drinking occasions (excluding plain water); and consumption of five or more portions of fruit and vegetables per day. Secondary outcomes relating to dental health are: the presence of dental caries; the number of dental caries symptoms; and treatment received for dental caries.

Self-reported pupil data will be collected in school, during two timetabled sessions approximately 1–4 weeks apart. Pupils will complete an online survey at each session followed by a 24-hour recall dietary assessment. The first and second sessions will be facilitated by trained researchers and classroom teachers, respectively. An alternative activity will be provided for non-participating pupils.

###### Dietary intake assessment

Dietary intake will be measured using Intake24, an online self-completion 24-hour dietary recall tool based on the multiple pass method, which has been shown to be the most accurate for assessing adolescent dietary intake.^27^ Compared with interviewer-led recall, Intake24 underestimated energy intake by just 1% in this age group, and differences in mean macronutrient/micronutrient intakes between the two methods were within 4%.^28^

Nutrient analysis of Intake24 data uses the National Diet and Nutrition Survey food database containing over 2300 foods linked to the UK Nutrient Databank codes.^29^ Intake24 piloting, community nutritionist consultation and literature review identified food/drinks commonly consumed by minority ethnic groups but not included in this database (n=63), which were added to Intake24. Nutritional data for these items were obtained through matching to existing items in Intake24 or from other existing food composition sources.^30 31^ Photographs are used for portion size estimation, a method which has shown good agreement with 4-day weighed intakes in adolescents.^32 33^

###### Assessment of dental caries experience

We will use validated self-report measures from the national Child Dental Health Survey^2^ to assess dental caries symptoms in the last 3 months and treatment received in the last 24 months. Self-reported tooth brushing frequency data will also be collected.

###### Other pupil data collection

Pupils will be asked to provide their age, sex, ethnicity, postcode (for mapping to Index of Multiple Deprivation (IMD) scores and exposure to fluoridated water), usual lunch type (school-provided vs home-packed), usual mode of travel to/from school and sleep/wake times for the previous night. Pupils will also complete the Child Health Utilities 9-Dimension (CHU-9D) questionnaire, a utility-based health-related quality of life questionnaire,^34^ for use within the economic evaluation.

##### Data collection tool piloting

The school staff, governor, pupil and parent surveys, the adapted Intake24 and the observation tool were piloted with the relevant target groups. The tools were revised in line with the feedback obtained.

#### Data analysis

##### Preliminary development of a school typology

Using the logic model (figure 1) as a guide, we will use data captured on SFS/SFP implementation and the school context to develop an initial typology of schools, which will reflect the degree of implementation of the SFS/SFP and other relevant local initiatives relating to food and healthy eating.

##### Analysis of pupil outcomes

Pupils will have a maximum of two 24-hour recalls for dietary intake measures. To summarise dietary outcomes, we will report the average value across the 2 days for each pupil. If only a single day is available, we will use data from that day only. Differences between the SFS mandated and SFS non-mandated school groups for both primary and secondary pupil outcomes will be assessed using multilevel linear models that account for clustering at the school and class level (and at the Multi-Academy Trust level if applicable). Models will include adjustment for propensity scores and pupil-level covariates (school year group, sex, ethnicity, IMD score and school-provided vs home-packed lunch). Models for dietary outcomes will use data recorded each day, allowing for the repeated outcome measures. Models for dental outcomes will be additionally adjusted for oral healthcare factors and water fluoridation exposure. We will also explore whether the associations between school SFS status and pupil outcomes differ across age, socioeconomic position (indicated by IMD score), or usual lunch type (school-provided vs home-packed) by adding the relevant interaction terms to the developed models. If more than 5% of data are missing from demographic variables, multiple imputation methods will be used and sensitivity analyses conducted.

If possible, within the group of schools which are not mandated to adhere to the SFS, we will undertake an exploratory analysis to examine differences in pupil outcomes between schools who have and have not voluntarily signed up to the SFS. In addition, we will develop further linear multilevel models to explore potential associations between the identified school types and pupil outcomes, again adjusting for clustering, potential pupil-level confounders and propensity scores, as described previously.

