Evaluation of the impact of the 2006 SFS on food provision and consumption has been conducted in primary (age 4–11 years) and middle (age 9–12 years) schools in the UK. Pre-SFS and post-SFS implementation comparisons showed improvements in overall dietary intake in pupils aged 4–7 years, but not in those aged 11–12 years.^10–12^ SFS implementation was good in primary schools but less so in middle schools.^10^ Evidence of SFS impact on secondary school pupils’ (aged 11–16 years) dietary intake is more limited. A study in 80 secondary schools compared school food provision in 2011 with that in 2004. They reported improvements in the nutritional content of school-provided food (in particular reduced confectionery availability) and pupils’ lunchtime food consumption, but did not examine total dietary intake.^13^

To date, the impact of the updated SFS or the SFP has not been evaluated. The way in which SFS legislation was introduced in England means that certain school types (including academies and free schools; 70% of secondary schools in England)^14^ that were set up between January 2010 and May 2014 are exempt from this legislation (although they can choose to voluntarily sign up to the standards), whereas schools of these types established before or after these dates are legally required to meet the SFS. This provides an opportunity to examine how a legal requirement to meet the SFS influences schools and their pupils. Given the lack of SFS/SFP evaluation in secondary schools, we aim to investigate their influence in these settings by comparing school food provision, sales, wider school factors related to food, pupil dietary intake and dental health across those mandated and not mandated to adhere to the current SFS. We will also explore variation in the implementation of the SFS and SFP recommendations and their economic impact.

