#### Data collection

##### Data capture on SFS and SFP implementation and the wider school context

A logic model setting out the processes by which the SFS/SFP are assumed to generate pupil health gains has been developed (figure 1). Briefly, we hypothesise that health gain materialises directly via a change in school food consumption and indirectly by curricular and other activities designed to change pupils’ dietary knowledge, attitudes and beliefs that impact on food consumption in and out of school. The extent to which the SFS/SFP achieve these health gains depends on their implementation within a school, which is influenced by key contextual factors (eg, school management, parental engagement and so on).

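### The main pupil models adjust for usual lunch type, a post-exposure variable plausibly on the policy pathway, so their coefficient may not be the total mandated versus non-mandated difference

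*Protocol article*

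**What the plan says.** Under Analysis of pupil outcomes, the protocol article states: "Differences between the SFS mandated and SFS non-mandated school groups for both primary and secondary pupil outcomes will be assessed using multilevel linear models". The covariates for these models are the propensity score and "pupil-level covariates (school year group, sex, ethnicity, IMD score and school-provided vs home-packed lunch". Lunch type is therefore in the main model for all three primary outcomes (free sugars at school lunch, while at school, and over 24 hours) and for every secondary outcome. The later models relating school type to pupil outcomes carry over the same adjustment. Lunch type also appears as an exploratory effect modifier, through interaction terms added to these models.

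Four other places bear on the choice:

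- Introduction, on the purpose: "This provides an opportunity to examine how a legal requirement to meet the SFS influences schools and their pupils".
- Introduction, on the School Food Plan (SFP): "One central aim was to increase school meal uptake, as higher demand enables better quality meals to be served at a lower cost".
- Data capture on SFS and SFP implementation and the wider school context, on the mechanism: "we hypothesise that health gain materialises directly via a change in school food consumption".
- Other pupil data collection, where pupils are asked for "usual lunch type (school-provided vs home-packed), usual mode of travel to/from school".

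**The concern.** Adjusting for a variable that the exposure can change does not estimate the total effect of that exposure. Whether a pupil eats a school lunch is plausibly one route by which food policy reaches diet. Holding lunch type fixed takes that route out of the comparison.

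The stake is how the primary result is read. If the policy draws pupils to school lunches and these contain less free sugar than packed lunches, part of the benefit is adjusted away. If restrictions push pupils towards packed lunches with more free sugar, that harm is adjusted away. In addition, if an unmeasured trait such as a liking for sweet food affects both lunch type and sugar intake, the adjusted coefficient need not equal the direct effect either.

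**Working it through.** **Order of events.** Under Sampling, SFS status rests on the date of academy or free school status. Usual lunch type is reported by pupils in the study survey. A current pupil's lunch choice cannot have caused the school's conversion date, so lunch type is post-exposure.

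**Target.** The Introduction asks how the legal requirement influences schools and pupils, and uses the mandate comparison to study both SFS and SFP. That is a total contrast. Nothing in the article says that an effect at fixed lunch type is wanted.

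**Scale: the plan's own sample size.** Inputs from Sample size calculation: difference 4 g, SD 11, ICC 0.1, 45 pupils per school, 90% power, 5% significance (two-sided assumed).

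- Individually sampled: 2 × [11 × (1.960 + 1.282) / 4]² = 158.9 per group.
- Design effect: 1 + 44 × 0.1 = 5.4.
- 158.9 × 5.4 = 858.2, so 859 pupils per group; 858.2 / 45 = 19.07, so 20 schools.

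The plan states 990 pupils and 22 schools per group, more than its inputs require. That is conservative and has no bearing on this point. At the stated size the standard error is 11 × √(2 × 5.4 / 990) = 1.149 g, and power for 4 g is 93.6% (normal) or 92.5% (t).

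**Distortion formula.** Let d be the change in the share of pupils taking school lunch that the policy causes, and g the free-sugar content of school-provided minus home-packed lunch. With no unmeasured common cause of lunch type and intake:

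adjusted coefficient = total effect - d × g

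The documents give neither d nor g. The values below are assumptions, with the total effect set at -4 g.

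| d (points) | g (g) | d × g (g) | Adjusted coefficient (g) | Power at that value |
|---|---|---|---|---|
| 0 | any | 0 | -4.00 | 93.6% |
| +5 | -5 | -0.25 | -3.75 | 90% |
| +10 | -5 | -0.50 | -3.50 | 86% |
| +10 | +5 | +0.50 | -4.50 | 97.5% |
| -10 | -5 | +0.50 | -4.50 | 97.5% |
| +20 | -10 | -2.00 | -2.00 | 41% |
| +20 | +10 | +2.00 | -6.00 | 99.9% |

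Power uses the 1.149 g standard error throughout, ignoring any gain in precision from the covariate.

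**Simulation check.** 44 schools of 45 pupils, ICC 0.1, SD 11, 2000 replicates, least-squares coefficients averaged; Monte Carlo error about 1.149 / √2000 = 0.03 g.

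| d (points) | g (g) | Without lunch type (g) | With lunch type (g) |
|---|---|---|---|
| 0 | -5 | -4.01 | -4.00 |
| +10 | -5 | -4.00 | -3.51 |
| +10 | +5 | -4.01 | -4.51 |
| +20 | -10 | -3.98 | -1.99 |
| +20 | +10 | -4.04 | -6.04 |
| +10 | -5, with common cause | -4.02 | -3.70 |

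In the last row an unmeasured trait raises the chance of school lunch by 15 points and intake by 3 g per SD. The adjusted value, -3.70 g, is then neither the total effect (-4.0 g) nor the direct effect (-3.5 g).

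**The case against.** The case for the current model has four parts.

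1. **The uptake aim belongs to another policy.** It is the SFP's, and the SFP is non-statutory; the exposure is the SFS mandate. A reader might infer that the mandate is meant to raise uptake, but the article does not say so. This weakens the evidence without removing it: the study uses the mandate contrast to examine SFS and SFP together, and the school-type models concern SFS/SFP implementation directly.
2. **The mechanism sentence does not establish mediation through lunch type.** A change in school food consumption could mean better food for pupils who already eat school lunch, and adjustment leaves that intact. The logic model figure is not available to check. Nor does collecting uptake ("To assess school lunch uptake, schools will be asked to provide their routinely collected school meal uptake data") show that it is regarded as a consequence of the mandate; in the same section it serves as an adjustment factor for food sales. This stands: the pathway is plausible, not demonstrated.
3. **Lunch type may stand in for family background.** The study is observational, the pupil data listed do not include individual free-school-meal eligibility (it enters only as a school proportion in the propensity score), and IMD is derived from postcode. Dropping lunch type could lose some control of confounding. This also stands, and it is why the adjusted model should be kept as a sensitivity analysis.
4. **The interaction analysis already handles lunch type.** It gives contrasts within lunch types and is exploratory. It does not supply the overall difference.

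**Conclusion.** The point holds in conditional form. The only main model specified adjusts for a post-exposure variable that plausibly lies between the policy and intake, while the stated interest is the overall influence of the mandate. If the policy makes school-lunch uptake differ between the groups, and the two lunch types differ in free sugars, the coefficient is not the total difference.

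A reader might go further and conclude that the primary result is biased, or biased towards no effect. The documents support neither. With equal uptake there is no distortion, and the sign depends on two quantities that are not given. Against the 4 g planning difference, a 10-point shift with a 5 g gap moves the estimate by 0.5 g (12.5%), or by about 0.3 g with the common cause modelled above. A 2 g change needs a 20-point shift and a 10 g gap. All these figures are illustrative. Because the direction is unknown, the adjustment cannot be defended as conservative. This should be fixed, but it does not invalidate the design.

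**What to change.** Make the primary model for each pupil outcome the one without lunch type. Retain the propensity score, year group, sex, ethnicity, IMD score, the planned clustering terms and, for dental outcomes, the extra covariates already listed.

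Report the lunch-type-adjusted model beside it as a labelled sensitivity analysis, stating that it can be read as a direct effect only if lunch type and intake share no unmeasured cause. Keep the lunch-type interaction as exploratory. Apply the same rule to the school-type models. Settle the change before the outcome data are analysed.

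The cost is a change of wording and one additional reported model, with no new data. There is a small loss of precision, and the primary model gives up lunch type as a possible proxy for pupil background; the sensitivity model shows whether that matters.
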